#### Randomization methods (generation of a random sequence)

Chiropractors within recruited practices meeting the inclusion criteria will be randomly allocated to receive either the KT strategies plus practice guidelines for the intervention group or practice guideline alone for the control group. Randomization will be done in a 1:1 ratio to the intervention and control groups using Stat Trek’s Random Number Generator. A research assistant independent of the study will generate, implement, and protect the randomization sequence.

#### Concealment of the allocation sequence

The allocation procedure will be conducted by a researcher using http://stattrek.com/statistics/random-number-generator.aspx. We will provide the ID numbers representing each recruited participant, and he/she will inform us whether the participant is allocated to the intervention or control group. Results will be communicated to the study coordinating unit. Thus, strict separation will be maintained between the code sequence generator and the study coordination personnel.

#### Blinding

Investigators not involved in the delivery of the intervention and the study statistician will be blinded to group allocation until the statistical analysis has been completed. Participating chiropractors will be aware of the KT interventions they are receiving/implementing; otherwise, they will not be explicitly informed of their assigned groups. Participating chiropractors will be instructed not to tell their patients about their KT interventions so as to maintain patient blinding. Participating chiropractors will also be kept blind to all study hypotheses.

### Data collection and management

#### Retention

Follow-up, in terms of both attended appointments and completion of questionnaires, will be assessed at the end of the study.

#### Logistics of multicentre procedures

Challenges in recruiting patients across practices will highlight possible difficulties with implementing a multicentre trial. To increase the likelihood of successful recruitment, participating chiropractors will be encouraged to appoint a single staff member who will be responsible for local trial operationalization and recruitment.

### Statistical analysis

The main analysis will focus on descriptive statistics relating to feasibility to estimate likely recruitment and retention rates, adherence to the intervention, and provide key parameters, e.g. effect size needed to decide on a primary outcome and to estimate the sample size for a full-scale study. Also, we will estimate the potential efficacy of the intervention on adherence to the recommended multimodal approach for NSNP and on patient outcomes of pain and disability. Instead of calculating an average response on each measure for each group and comparing means between groups, this study will identify the proportion of people in each group making a treatment response, which will then be compared between groups. Each person will be classified as having made a response, a deterioration, or no change on each measure based on a change equal to or greater than the MCID published or recommended for that measure. Table 4 provides the summary of this analysis.

**Table 4 Tab4:** Statistical analysis

Construct	Measure	Measurement scale
Feasibility of recruitment, retention, and data completion (both chiropractors and patients)	Recruitment and retention rates, missing data	Descriptive statistics: mean and SD for continuous variables and proportions for categorical variables
Chiropractor process outcomes		
Adherence rate	Single indicators	Continuous data (number of DCs adhering to the intervention per number of eligible participants)
	Composite	Count of indicators reaching “success” threshold
Behavioural	Level of knowledge and self-efficacy	5-point Likert scale (from 1 = strongly agree to 5 = strongly disagree), ordinal
Patient health outcomes		
Pain	Visual analogue scale	Self-rated level of pain on 11 points, continuous
Disability	Neck Disability Index	Scale range and subscales: 10 items in total; each item is scored from 0 to 5 (“0” = no disability and “5” = full disability) for a total of 50
Satisfaction with care	Questionnaire	Self-rated satisfaction with care measured on the short-form questionnaire rated on a 5-point Likert scale from “very satisfied” to very “dissatisfied”
Potential efficacy	Post-intervention between groups	Normal approximation to the binomial

For the efficacy potential analysis, we will estimate the proportion of chiropractors who endorsed a higher knowledge level post-intervention in the control group and use this as the basis for calculating the probability of achieving a response more extreme than this in the intervention group using the normal approximation to the binomial distribution (stattrek.com). For example, if 2 of 15 participants in the control group endorse a higher knowledge level, this yields an expected “success” proportion of 0.13. Based on this expected proportion or probability, if 5 or more of the 16 chiropractors in the intervention group endorsed a higher knowledge response, the probability of this occurring by chance would be 0.047. This approach will be used for each of the single indicator variables under study here (i.e. knowledge and self-efficacy).

We will use generalized estimating equations (GEEs) to adjust for anticipated correlation in measurements of observations within practices (clusters). For pain and disability, GEE will be used separately for each of these outcomes and to examine for any effect of our complex intervention over time (the follow-up period). This method extends the standard regression analysis to account for any covariance between repeated measurements of pain and disability (as separate outcomes) over time, in addition to accounting for anticipated correlation of observations within practices.

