**Methods/design:**

The design is a cluster-randomized controlled pilot and feasibility trial. Chiropractors in private practice in Canada will be approached to participate in the study. Thirty consenting chiropractors will be randomized to receive either a theory-based educational intervention in the experimental group or simply a printed copy of the guideline in the control group. Each chiropractor will recruit five neck pain patients (a total of 150 patients) into the study. Development of the multifaceted intervention was informed by the results of a related qualitative study based on the Theoretical Domains Framework and consists of a series of three webinars, two online case scenarios, a self-management video on Brief Action Planning, and a printed copy of the practice guideline. *Primary feasibility outcomes* for both chiropractors and patients include rates of (1) recruitment, (2) retention, and (3) adherence to the intervention. A checklist of proxy measures embedded within patient encounter forms will be used to assess chiropractors’ compliance with guideline recommendations (e.g. exercise and self-care prescriptions) at study onset and at 3 months. Secondary outcomes include scores of behavioural constructs (level of knowledge and self-efficacy) for recommended multimodal care. *Clinical outcomes* include pain intensity and neck pain-specific disability. Analyses from this study will focus on generating point estimates and corresponding 95 % confidence intervals for parameters of a priori interest (recruitment, retention, adherence, pain intensity, Neck Disability Index).

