## Methods/design

### Design

This is a pilot cluster-randomized, two-arm, parallel-group controlled trial with a 1:1 allocation ratio. A cluster-randomized design has been chosen to avoid contamination between intervention and control arms by individual patients who would potentially be served by the same chiropractor in a non-cluster design. In addition, cluster-randomized trials offer logistical convenience when implementing certain interventions such as training, feedback, and supervision programmes, which are easier to administer to groups rather than individuals [32].

The study will test the feasibility and impact on protocol adherence and patient outcomes of two methods of delivering an educational intervention: (1) a KT complex intervention (theory-based KT intervention that includes three webinars, two case scenarios followed by a quiz, and Brief Action Planning) plus dissemination of practice guidelines for the intervention group and (2) passive dissemination of a practice guideline alone for the control group.

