#### Recruitment of patients

Participating chiropractors will each recruit up to five consecutive new patients with neck pain. A recruitment/advertisement notice will be posted in each participating chiropractor’s waiting room. The expected recruitment of 5 patients within 3 months is reasonable assuming an average practice volume of 85 patient visits per week per chiropractor, of whom 25 % are expected to have neck pain [6].

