Expected adherence to multimodal care by patients will also be assessed at baseline using a specific questionnaire item (e.g. “I intend to perform the neck exercises that were prescribed for my condition”). Furthermore, compliance with guideline recommendations at the patient level will be measured using a checklist documenting the extent of their confidence in managing most of their health problems, the type of help received from their treating chiropractor, and the use of exercise and self-care prescriptions, as well as their levels of compliance with recommended exercises (Additional file 1). Furthermore, patient-related health outcomes will be collected at baseline and at 3 months through the use of questionnaires to measure symptoms, impairment, activity interference at home and at work, general quality of life, and satisfaction with care (PSQ-18). The minimal clinically important difference (MCID) in the 10-cm VAS pain score will be measured as the mean difference between current and baseline scores among patient participants who report feeling either “a little worse” or “a little better” in terms of their global self-perceived change. Otherwise, a 10 % change from baseline will be considered minimal change, while a 30 % change from baseline will be considered a substantial and clinically important change [37].

The Neck Disability Index (NDI) is a 10-item self-administered questionnaire, scored from 0 to 50 with a higher score representing more disability. A score of 0 to 4 represents no disability, a score >35 represents complete disability, and a score >25 represents severe disability. An absolute change of 10 points or relative change of 20 % on the NDI will be considered clinically important [38].

Feasibility to conduct a larger study will also be determined by estimating the effect size (and subsequently, the anticipated sample size) needed for a future main trial. Challenges encountered by participating clinicians while conducting the trial will be assessed by administering an end-of-study questionnaire and conducting interviews. An open-ended question will be used to elicit the chiropractors’ experiences (challenges or facilitators) encountered while trying to comply with the guideline recommendations.

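### The pilot's observed effect size is to guide the choice of primary outcome and set the main-trial sample size, but this trial estimates it too imprecisely for either use

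*Protocol article*

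**What the plan says.** The Statistical analysis section calls the main analysis descriptive, then names one parameter for planning the next trial: the "effect size needed to decide on a primary outcome and to estimate the sample size for a full-scale study". The Measures section shows that this means the effect estimated here. It says feasibility of the larger study is to be judged in part "by estimating the effect size (and subsequently, the anticipated sample size) needed for a future main trial".

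The planned sample is given in the Abstract: "Thirty consenting chiropractors will be randomized to receive either" the intervention or the control, and "Each chiropractor will recruit five neck pain patients (a total of 150 patients) into the study". Five is a ceiling, since "Participating chiropractors will each recruit up to five consecutive new patients with neck pain". The Design section describes a "two-arm, parallel-group controlled trial with a 1:1 allocation ratio". Recruitment of chiropractors justifies the number approached by expected recruitment and retention rates. No target precision for an effect is stated. Trial status reports that 45 chiropractors have in fact been randomized.

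The Abstract also promises point estimates with 95% CIs for "parameters of a priori interest (recruitment, retention, adherence, pain intensity, Neck Disability Index"). No text links those intervals to the sizing of the main trial.

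**The concern.** A pilot of this size can show whether chiropractors and patients can be recruited and kept, and roughly how variable the outcomes are. It cannot locate a plausible treatment effect with useful accuracy. Required sample size varies with the inverse square of the assumed effect, so modest error in the estimate becomes very large error in the main-trial size. An estimate that is high by chance yields an underpowered main trial. One that is low by chance yields a needlessly large one. Choosing the primary outcome from the same estimates adds a second use that the data cannot support. The stated purpose of the pilot is to inform the design of a full cluster trial, so this bears on its main product.

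**Working it through.** **The plan's own figures.** Recruitment of chiropractors: 200 × 0.20 = 40 agreeing, and 40 × 0.80 = 32 retained, close to the required 30. Patients: 30 × 5 = 150. These reproduce, but they concern recruitment and retention and not precision.

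**Inputs from the protocol.** 1:1 allocation; 15 clusters per arm planned; 45 randomized, so 22.5 per arm on average; m = 5 patients per cluster (the ceiling).

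**Assumptions, not in the protocol.** ICC 0 to 0.20; two-sided 5% level and 80% power for the main trial, with five patients per cluster; true effect 0.30 SD where one is needed; no baseline adjustment; no patient loss.

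**Step 1: precision.** Design effect DEFF = 1 + (m − 1) × ICC, and SE = √(2 × DEFF / (k × m)) for k clusters per arm.

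At ICC 0.05, DEFF = 1.2. For k = 15, SE = √(2.4/75) = 0.179. For k = 22.5, SE = √(2.4/112.5) = 0.146. The 95% half-widths (1.96 × SE) are:

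| Clusters per arm | ICC 0 | ICC 0.05 | ICC 0.10 | ICC 0.20 |
|---|---|---|---|---|
| 15 (planned) | 0.32 | 0.35 | 0.38 | 0.43 |
| 22.5 (45 randomized) | 0.26 | 0.29 | 0.31 | 0.35 |

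For responder proportions, the comparison that the Statistical analysis section prefers to means, the half-width is 1.96 × √(2p(1 − p) × DEFF / (k × m)). With p from 0.3 to 0.5 and ICC 0 to 0.10 it is 0.15 to 0.19 for k = 15 and 0.12 to 0.15 for k = 22.5. For a continuous outcome measured on the chiropractors themselves, it is 1.96 × √(2/15) = 0.72 SD planned, or 1.96 × √(2/22.5) = 0.58 SD with 45.

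**Step 2: what this does to the main-trial size.** Patients per arm = 2 × (1.96 + 0.84)² / d² × 1.2. An observed 0.30 at ICC 0.05 with 45 clusters has the CI 0.30 ± 0.29, about 0.01 to 0.59.

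- d = 0.59: about 54 per arm
- d = 0.30: about 209 per arm
- d = 0.10: about 1,884 per arm
- d = 0.01: about 188,000 per arm, effectively unlimited

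With the planned 30 clusters the CI is about −0.05 to 0.65, so the lower limit gives no finite size and the upper gives about 45 per arm.

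**Step 3: power of a main trial sized on the pilot estimate.** If the true effect is 0.30 and the main trial is sized on a positive estimate x, its actual power is Φ(2.80 × 0.30/x − 1.96).

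- Power is below 80% whenever x exceeds 0.30. Among positive estimates this is 0.5/0.980 = 51% with 45 clusters and 0.5/0.953 = 52% with 30.
- Power is below 50% whenever x exceeds 2.80 × 0.30/1.96 = 0.429. With 45 clusters, (0.429 − 0.30)/0.146 = 0.88, an upper tail of 0.189, and 0.189/0.980 = 19%. With 30 clusters, 0.129/0.179 = 0.72, an upper tail of 0.236, and 0.236/0.953 = 25%.

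The first figure is near one half for any unbiased estimate. The second shows how severe the shortfall can be.

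**Step 4: conditional on preferring the larger of two observed effects.** For two outcomes with the same true effect 0.30 and correlation ρ between their estimates, the mean of the larger is 0.30 + SE × √((1 − ρ)/π). With 45 clusters at ICC 0.05:

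- ρ = 0.8: 0.30 + 0.146 × 0.252 = 0.34
- ρ = 0: 0.30 + 0.146 × 0.564 = 0.38

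With 30 clusters the range is 0.345 to 0.40.

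**The case against.** Five objections deserve an answer.

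- **More clusters than planned.** With 45 chiropractors randomized, the interval is narrower than the planned 30 would give. This stands, and the main figures here use 45. The interval is still about as wide as the effect it surrounds, and five patients per chiropractor is a ceiling.
- **No rule to pick the largest effect.** A reader might infer that the selected outcome's effect will be biased upward. Deciding on a primary outcome from effect size suggests this, but the protocol states no such rule. The bias in Step 4 is therefore conditional. The imprecision in Steps 1 to 3 does not depend on it.
- **No effect-size stopping criterion.** A reader might infer that a low estimate would lead the main trial to be abandoned. The protocol does not support that: the feasibility criteria in Table 1 concern recruitment, adherence and retention, and effect size is only an additional consideration without a threshold.
- **Unlisted planning parameters.** A reader might fault the article for not listing the SD and ICC. That is not a finding. Effect size is introduced only as an example, clustering is handled by generalized estimating equations, recruitment and retention are listed, and a condensed article may leave the rest to fuller documents.
- **Descriptive reporting already planned.** The 95% CIs for pain and the Neck Disability Index are promised. This helps interpretation, but it does not alter the stated use of the effect size for outcome choice and sizing.

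**Conclusion.** The point holds. As worded, the Measures and Statistical analysis sections give the pilot's observed effect a role in choosing the primary outcome and sizing the main trial, and its 95% half-width is about 0.26 to 0.35 SD with the 45 clusters randomized (0.32 to 0.43 with the 30 planned). The conclusion does not need clustering, since it holds at ICC 0. It also holds for responder proportions and, more strongly, for outcomes measured on chiropractors.

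The power and sample-size figures rest on an assumed true effect of 0.30, ICC 0.05, 80% power and full clusters of five. Smaller clusters or attrition would widen the intervals. An upward bias from outcome selection is possible but not established by the text. Correction is advisable: nothing in the pilot's conduct has to change, but the rule as written would give a worse main-trial design.

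**What to change.** Reword the two sections so that:

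- the primary outcome of the main trial is chosen on relevance to the main-study question, completeness of measurement and retention, not on the observed effect;
- the main trial is sized on a separately justified between-arm important difference, in means or in responder proportion, not on the pilot point estimate;
- the pilot supplies the SD or control response rate, the ICC with its uncertainty, the achieved cluster size and attrition;
- the between-arm effect is reported with its 95% CI as descriptive only.

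The thresholds in the Measures section should not be used directly as that between-arm difference. They describe change within a patient, the pain threshold is partly to be estimated from this trial's own patients, and the Neck Disability Index has two alternatives. As an illustration, if the SD of the index were 10 points (an assumption), a 10-point target would mean d = 1.0 and only about 19 patients per arm (2 × 2.80² × 1.2 = 18.8), which could itself leave the main trial underpowered.

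The cost is a change of wording and a little extra analysis of data already planned. The downside is that the main-trial size then rests on a judgement of what difference is important, which has to be argued openly.

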### Measures

The key feasibility outcomes of interest include (1) study recruitment/participation, (2) adherence to the intervention, (3) study retention, and (4) KT intervention effectiveness potential. Table 1 provides the different criteria for defining the outcomes derived from items (1) to (4) above. Table 2 further summarizes the feasibility outcomes, sources of measurement, and timing of administration.

**Table 1 Tab1:** Criteria to assess feasibility

Construct	Parameter
	Eligibility proportion
Chiropractors	
Recruitment	Trial acceptance rate: >20 % agree to participate within 4 weeks
	Target population = 40 (assuming an 80 % retention rate)
Adherence to protocol	>90 % of participants will complete all 3 webinars, associated quizzes, 2 clinical vignettes, and a self-management learning module
Retention	80 % of participants will complete 3 months of patient follow-up
Patients	
Recruitment	Trial acceptance rate: 5 patients within 6 weeks of recruitment notice
	Target population = 150
Adherence to protocol	95 % will attend regular treatment sessions twice/week
	>80 % will comply with prescribed home exercise and physical activity
Retention	>80 % will complete patient encounter forms (VAS, NDI, and PSQ-18) and follow-up at 3 months

**Table 2 Tab2:** Outcome measures

Outcome	Source	Description of measures	Data collection time points	
Feasibility				
Recruitment	Chiropractors and patients	Measured as a proportion of chiropractors and patients potentially eligible for participating	Initial stage	
		Eligibility rate = number of eligible chiropractors and patients divided by the number of invited chiropractors or patients		
		Participation rate = number of chiropractors and patients agreeing to participate divided by number of eligible chiropractors and patients		
Adherence to protocol	Chiropractors	For those randomized to intervention arm, measured through the rates of attendance of all 3 webinars, associated quizzes, completion of 2 clinical vignettes, and the self-management learning module	Within 6 weeks of assignment	
	Patients	Rate of adherence to follow-up visits, prescribed home exercise, and physical activity	Baseline	3 months
Adherence perception (knowledge and self-efficacy)	Chiropractors and patients	Completion of questionnaires	Baseline	3 months

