### Trial status

At the time of writing, 45 chiropractors have agreed to participate in the study and have been randomized to the intervention and control groups. Participants have started recruiting neck pain patients. Results are expected in May 2016.

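### The plan sets unreconciled analyses for pain and NDI (responder proportions, an unrestricted normal-approximation row in Table 4, and a clustered GEE) and does not say which one yields the promised 95% intervals

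*Protocol article*

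**What the plan says.** Three statements in the Protocol article bear on how pain and disability will be compared between arms.

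- **Statistical analysis, opening paragraph.** Potential efficacy covers pain and disability as well as adherence to multimodal care. The next sentence sets the method: "Instead of calculating an average response on each measure for each group and comparing means between groups", the study compares the proportion of people in each arm who respond. Each person is classed on every measure as responding, deteriorating or unchanged, according to the MCID.
- **Table 4**, presented as the summary of that analysis. It lists pain as continuous. Its only between-group method is in the last row, for potential efficacy: "Normal approximation to the binomial". The row names no outcome and follows directly after the patient outcomes.
- **Statistical analysis, text after Table 4.** The normal approximation is explained for the chiropractors' knowledge level and said to be used for the single indicators, namely knowledge and self-efficacy. For pain and disability, "GEE will be used separately for each of these outcomes", to look for an intervention effect over follow-up. The GEE is meant to handle both the repeated measurements and the correlation within practices.

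The abstract promises point estimates and 95% confidence intervals for pain intensity and NDI. Measures and Statistical analysis both say the pilot should provide an effect size and a sample size for the full trial.

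**The concern.** The first statement rules out comparing means on each measure. The third describes regression on repeated pain and disability measurements, which most naturally means the scores. An analyst could follow either and produce different estimates for the same outcome, on different scales. The choice would then be open after the data are seen.

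The Table 4 row adds a second ambiguity. Read alone, it puts an unclustered binomial method on patients who are nested in chiropractors, and that would make the intervals too narrow.

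The stake is the pilot's product. Planning a cluster trial on VAS or NDI scores needs a mean difference, an SD and an ICC. A responder comparison alone gives neither of the first two and uses the data less efficiently.

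**Working it through.** **Inputs from the article**

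- Planned clusters (abstract): "Thirty consenting chiropractors will be randomized to receive either a theory-based educational intervention".
- Table 1 target for chiropractors: "Target population = 40 (assuming an 80 % retention rate".
- Trial status: "At the time of writing, 45 chiropractors have agreed to participate in the study and have been randomized".
- Cluster size (abstract): "Each chiropractor will recruit five neck pain patients (a total of 150 patients) into the study".
- Allocation (Design): "two-arm, parallel-group controlled trial with a 1:1 allocation ratio".

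**Assumptions, because the article gives no value:** ICC 0.01 to 0.10; responder rate 30% to 50% (0.40 in the simulations); normally distributed scores for the information calculation.

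**1. The plan's own figure.** No power or precision figure is given for pain or NDI. The only worked number is for chiropractors' knowledge: 5 or more of 16 against an expected proportion of 0.13, stated as 0.047. The exact binomial tail is 0.0471, so 0.047 is reproduced. The normal approximation named for it gives 0.015, or 0.036 with continuity correction. That is a separate matter of the example not matching its label. It does not bear on pain or NDI.

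**2. The statements side by side.** A response defined by change from baseline exists once per patient at 3 months, so it is not a repeated measurement. The GEE text speaks of covariance between repeated measurements over time. The natural reading is therefore a model of scores, which the opening paragraph sets aside. GEE can also be fitted to a binary outcome, so the two can be reconciled, but the article does not do so.

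**3. Information kept by a responder cut.** Relative efficiency is phi(z)^2 / [p(1 - p)], where z is the normal quantile at p.

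- p = 0.5: 0.3989^2 / 0.25 = 0.637; 150 patients carry the information of about 95.
- p = 0.3: 0.3477^2 / 0.21 = 0.576; 150 patients carry the information of about 86.

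**4. If the Table 4 row were applied to patients.** Design effect DE = 1 + (5 - 1) x ICC. True two-sided error = 2[1 - Phi(1.96 / sqrt(DE))].

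| Assumed ICC | DE | True error at nominal 5% | Simulated coverage of an unclustered two-proportion 95% interval, 30 clusters |
|---|---|---|---|
| 0.01 | 1.04 | 5.5% | 94.0% |
| 0.05 | 1.20 | 7.4% | 91.9% |
| 0.10 | 1.40 | 9.8% | 89.1% |

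**5. The GEE with a limited number of clusters.** With equal cluster sizes and an identity link, the GEE estimate is the difference between arm averages of the cluster means. For k clusters per arm, the uncorrected sandwich variance is (k - 1)/k times the unbiased one. Coverage with a z reference is therefore P(|t| <= 1.96 x sqrt((k - 1)/k)) on 2k - 2 degrees of freedom.

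| Clusters | k | Adjusted cut-off | Coverage by formula | Simulated, uncorrected (40,000 trials per setting) | Simulated, corrected with t |
|---|---|---|---|---|---|
| 24 (80% of 30) | 12 | 1.877 | 92.6% | 92.5-92.8% | 94.8-95.1% |
| 30 | 15 | 1.894 | 93.1% | 93.0-93.4% | 94.7-95.2% |
| 44 (near the 45 randomized, equal arms) | 22 | 1.915 | 93.8% | 93.7-93.8% | 94.9-95.0% |

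The simulated ranges span continuous and binary outcomes and the three ICCs.

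**6. Price of the correction.** Interval width relative to uncorrected z is t x sqrt(k/(k - 1)) / 1.96. At 30 clusters this is 2.048 x sqrt(15/14) / 1.96 = 1.08, and at 44 clusters 2.018 x sqrt(22/21) / 1.96 = 1.05. Intervals widen by about 8% and 5%.

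**The case against.** The strongest reply is that the text after Table 4 already settles most of this. It confines the normal approximation to knowledge and self-efficacy. Those are measured on the chiropractor, who is the unit randomized, so patient nesting does not arise. It gives pain and disability a GEE that accounts for clustering within practices. On that reading the Table 4 row is only poorly labelled, and the error rates in step 4 describe an analysis that the text does not assign to pain or NDI. This stands: those rates are conditional on following the table instead of the text.

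A reader might also infer that neither analysis can give valid intervals. The documents do not support that. They name no variance estimator, and that detail may properly sit in an analysis plan that is not shown. Even an uncorrected sandwich loses only about 2 points of coverage at 30 clusters. Nor is the trial tied to about 30 clusters: Table 1 aims for 40 and 45 were already randomized. At 44 the loss is about 1 point, and 80% of 45 would still leave 36.

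Calling the analyses incompatible would likewise go too far. Responder proportions could accompany a GEE on scores, or be modelled by GEE. The 58-64% figure applies only if responders are the sole analysis.

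Finally, this is a feasibility study whose main analysis is descriptive, and Table 1 sets no threshold on pain or NDI effects. That limits the severity. It does not answer the gap, because the article promises intervals for these two outcomes and wants an effect size for the main trial.

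**Conclusion.** The point holds as an unreconciled specification. The opening paragraph replaces means by responder proportions on each measure, Table 4 leaves its one between-group method unrestricted, and the later text fits a clustered GEE to repeated pain and disability measurements. The article does not say which of these gives the 95% intervals for pain and NDI.

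If responders alone were used, no mean difference or SD would be available for the main trial, and about 36-42% of the information would be lost, assuming normal scores and 30-50% responders. If the Table 4 row were applied to patients, error would rise from 5% to about 5.5-9.8% at assumed ICCs of 0.01-0.10 with five patients per chiropractor. The documents do not establish that patient outcomes will be tested without regard to clustering, or that the GEE intervals will be invalid.

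This should be corrected, but it does not threaten the feasibility aims.

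**What to change.** - Name one main analysis for VAS and for NDI: a cluster-adjusted model of the 3-month score on arm and baseline score, with chiropractor as the cluster. Report the mean difference, its 95% interval, the SD and the ICC.
- State a small-sample variance correction with a t reference, for example a Mancl-DeRouen GEE on clusters minus 2 degrees of freedom, or a mixed model with Kenward-Roger. In the equal-cluster check, a corrected sandwich with t restored coverage to about 95% at 24, 30 and 44 clusters.
- Keep the MCID responder proportions as a secondary summary, estimated in the same clustered framework, and reword the opening paragraph so that it no longer rules out comparing means.
- Restrict the normal-approximation row of Table 4 to the chiropractor-level indicators, in line with the text.

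The cost is wording and minor analysis work. Relative to an uncorrected GEE, intervals widen by about 8% at 30 clusters and 5% at 44. No new data are needed.
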